## Sample size

In a previous study using eye tracking glasses examining VA during neonatal resuscitation, in which the operator acted both as an airway manager and team leader. In this study operator spent 35% (SD 8) of time focused on the infant. With the presence of dedicated resuscitation leader, to improve the VA on the infant to 55% with 80% power and alpha error of 0.05, we will need to conduct 6 scenarios with 3 samples in each group (equalling 18 participants).

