## **Eye-tracking devices/glasses in medicine**

Eye-tracking is a method of observing an eye movement as a reflection of attentional behaviour. It is based on the concept that attention is focused to a particular location to

maintain attention on a point of interest. This concept is utilized in eye-tracking technology to capture gaze behaviour, which provides information about an individual's attention over points of interest and allocation over time. In recent years, it has been used in medical field and is a valuable tool in medical education by providing training and effective feedback.

To date, wearable eye-tracking glasses have been used in few neonatal and critical care studies. For example, modern wearable eye-tracking glasses have been assessed for usability in a delivery room simulation where focus of cognitive attention was successfully captured, and all wearers agreed they would wear the glasses during the resuscitation. Equally, those findings were replicated in another neonatal simulation study where eye-tracking glasses did not provide any discomfort and participants felt the technology easy to use during the simulation. Attempts to examine human factor have been investigated during neonatal intubation in the neonatal unit, which found 50% of visual attentions is directed away from the infant and the team when they used nonstandard communication. This highlights how eye-tracking device could be an effective tool to analyze human factors for improved medical training, but the study failed to examine task-cognitive load with presence of dedicated team leader and outcomes with use of structured checklist.

We hypothesize that there will be difference in situational awareness, workload, and performance when there is multi-tasking as compared to performing single dedicated role during neonatal care. Here we propose the use of wearable eye-tracking glasses to help standardise approaches to examine situational awareness inferred by objective data from examining human factors/behaviour. Additionally, this may help inform the impact of using standardised checklist and role allocation on multi-tasking, which will be useful in resource limited settings. Subsequently, this manuscript describes the protocol that will be used to evaluate these approaches in a pilot observational study.

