## **Study algorithm**

Each team will participate in two simulation scenarios (i) term and (ii) preterm. With 3 teams, there will be total of 6 simulation experiments. Each team will undergo one scenario with a team leader and another scenario without a team leader. The sequence in which each team is allocated with/without team leader would be alternating with each team. For example, if team #1 starts with team leader for their preterm scenario, team #2 would participate same preterm scenario without team leader. This will ensure that both scenarios have an equal number of scenarios with and without a team leader.

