## Statistics

This is an exploratory study consisting of XXX groups. To the authors knowledge, there has yet to be a comprehensive analysis of VA with eye-tracking in neonatal simulations examining impact of a team lead with a checklist. However, there has been a pilot study using eye-tracking in neonatal resuscitation which used a dataset of 6 participant video-based eye-tracking recordings of 5mins duration. Therefore, our anticipated dataset size of 24 participants, will provide greater insight to examine VA behaviour differences and detect impact of a team lead with a standardised checklist. Data will be analysed in SPSS (v23, IBM) and R studio (R. RStudio, Boston, MA, USA). To conform to the exploratory nature of the work, descriptive statistics such as means, and ranges will be used here based on the number of participants stratified across 4 teams. Independent t-tests will further explore any observable differences. Those data will be complimented with simple plots. Anonymised data will be made available on reasonable request.

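### The 80% power claim for 3 samples per group leaves sidedness and the unit of analysis unstated; a two-sided independent t-test on one operator per scenario has about 64%

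*Protocol*

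**What the plan says.** The Sample size section takes its reference value from an earlier eye-tracking study in which one person both managed the airway and led: "In this study operator spent 35% (SD 8) of time focused on the infant". For an improvement to 55% it concludes that, "with 80% power and alpha error of 0.05, we will need to conduct 6 scenarios with 3 samples in each group", and it equates this with 18 participants. No formula, sidedness or definition of a sample is given.

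Other sections bear on how this should be read:

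- **Test.** Statistics says: "Independent t-tests will further explore any observable differences". It also describes the study as exploratory and mainly descriptive.
- **Hypothesis.** The introduction gives no direction: "We hypothesize that there will be difference in situational awareness, workload, and performance".
- **Design.** Study algorithm has three teams and six scenarios: "Each team will undergo one scenario with a team leader and another scenario without a team leader". That makes three scenarios per condition, with the same teams in both.
- **Who is measured.** The primary aim concerns the person at the airway, with and without a separate leader. Under Briefing, the airway operators are the ones prepared for the eye-tracker.
- **Counts.** Sample size gives 18 participants. Statistics gives 24 participants in 4 teams. Participants describes teams of four, and Simulation and Study algorithm use three teams, which makes 12 people.

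**The concern.** The planned comparison has very few observations. With 3 values per group an independent t-test has 4 degrees of freedom, and its two-sided 5% critical value is 2.78 rather than the normal 1.96. A size of 3 per group is what the large-sample formula gives for this effect, so the 80% needs checking against the t distribution.

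The power statement is the protocol's stated justification for six scenarios. If the true power is well below 80%, a non-significant result carries less information than the protocol suggests, and a reader could take it as firmer evidence against an effect of a dedicated leader than it is.

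**Working it through.** **Inputs.** Means 35 and 55 (difference 20 points), SD 8, power 80% and alpha 0.05 come from Sample size. The independent t-test comes from Statistics. Three operators per condition follow from Study algorithm and Briefing. The standardised difference is 20/8 = 2.5.

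**Reproducing the stated size.** Two routes lead to 3 per group.

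1. Two-sided normal approximation: n = 2 × (1.96 + 0.84)² / 2.5² = 2.51, rounded up to 3. Nominal power at n = 3 is Φ(3.06 − 1.96) = 86.5%, where 3.06 = 20 / (8 × √(2/3)).
2. One-sided 5% t-test, exact: df = 4, critical value 2.13, noncentrality 3.06, power 80.5%.

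**Two-sided 5% independent t-test, exact.** Power = P(|T| > critical value), with T noncentral t, df = 2n − 2 and noncentrality 20 / (8 × √(2/n)).

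| n per group | df | critical value | noncentrality | power |
|---|---|---|---|---|
| 3 | 4 | 2.78 | 3.06 | 63.6% |
| 4 | 6 | 2.45 | 3.54 | 83.6% |

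A simulation of the n = 3 case gave 63.8%. The smallest size that reaches 80% is therefore 4 per group. The unequal-variance (Welch) form of the test gives about 53% at n = 3.

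**Consequences at n = 3, two-sided.**

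- Risk of missing the planned effect: 100 − 63.6 = about 36%.
- Difference detectable with 80% power: 3.075 SD, and 3.075 × 8 = 24.6 points.
- Expected 95% confidence interval half-width: 2.776 × 8 × √(2/3) = 18.1 points.

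**If the same operators are compared across conditions.** A paired t-test on 3 pairs has df = 2 and critical value 4.30. The SD of the difference is 8 × √(2(1 − ρ)). The documents give no within-person correlation ρ, so it is shown over a range of assumed values.

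| assumed ρ | SD of difference | two-sided power |
|---|---|---|
| 0 | 11.3 | 40% |
| 0.3 | 9.5 | 51% |
| 0.5 | 8.0 | 62% |
| 0.7 | 6.2 | 79% |
| 0.75 | 5.7 | 85% |
| 0.8 | 5.1 | 90% |

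Power passes 80% at a correlation just above 0.7.

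**The case against.** **Sidedness.** A reader might infer that the 80% is simply wrong. The documents do not support that without a condition. Sidedness is never stated, the sample-size sentence speaks of an improvement, and a one-sided 5% t-test with 3 per group gives 80.5%, very close to the stated figure. This stands as a limit on the point. It does not remove the point: the hypothesis is worded as a difference, an unqualified alpha of 0.05 is conventionally two-sided, and a one-sided test would have to be stated.

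**Origin of the 3.** It is also tempting to say that the size came from the normal formula. That is inference. The protocol shows no formula, and two routes reach 3.

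**Meaning of a sample.** Six scenarios times three samples is 18, so three people may have been meant per scenario. The visual attention outcome table (Table S2) does list three roles. Counted that way there are 9 values per condition and nominal power exceeds 99%. The ambiguity is real and has to be resolved first. This reading does not rescue the claim, though: the primary aim and the 35% (SD 8) concern the operator, and members of one team are not independent observations.

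**Pairing.** If the same operators are compared and their values correlate strongly, 3 pairs could exceed 80%. That is possible, but the protocol assumes no correlation and names an independent test.

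**Exploratory status.** The study calls itself a pilot and exploratory, and no decision rule rests on a null result. This lowers the severity. It does not justify leaving a power figure in place that the named test may not have.

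**Conclusion.** The point holds conditionally. Assuming one airway operator per scenario, 3 per condition, SD 8 in both conditions and a two-sided 5% independent t-test with equal variances, power for the 20-point difference is about 64%, and 4 per group are needed (84%). The stated 80% is consistent with the protocol's inputs only under an unstated one-sided 5% test (80.5%). The normal approximation also clears it (86.5%) but cannot be relied on at 4 degrees of freedom. The gap is one observation per group, or about 5 points in detectable difference (24.6 against 20). Severity is moderate: the figure is the stated basis for the study size, but the analysis is declared exploratory.

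**What to change.** 1. State whether the test is one- or two-sided, and define the unit of analysis (for example, one airway operator per scenario).
2. Reconcile the 18, 24 and 12 participant counts and the 3 versus 4 teams across Sample size, Statistics, Participants, Simulation and Study algorithm.
3. With 3 per condition and an independent two-sided test, restate the figure along these lines: *3 operators per condition give about 64% power (two-sided 5% independent t-test) for a 20-point difference with SD 8; the difference detectable with 80% power is about 25 points.* If four teams are the real plan, each run once per condition, the figure is 4 per condition (8 scenarios) and 84%.
4. If the same operators are compared across conditions, base the statement on the paired test and show the assumed correlation and the range above.
5. Alternatively, drop the power claim, rely on the exploratory description already in Statistics, and give the expected 95% confidence interval half-width (about 18 points for 3 per group, treated as independent).

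The cost is rewriting one paragraph and aligning the counts elsewhere. No added recruitment is required unless the 80% is to be kept with a two-sided independent test. The restated power will look less favourable.

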## Statistics

This is an exploratory study consisting of XXX groups. To the authors knowledge, there has yet to be a comprehensive analysis of VA with eye-tracking in neonatal simulations examining impact of a team lead with a checklist. However, there has been a pilot study using eye-tracking in neonatal resuscitation which used a dataset of 6 participant video-based eye-tracking recordings of 5mins duration. Therefore, our anticipated dataset size of 24 participants, will provide greater insight to examine VA behaviour differences and detect impact of a team lead with a standardised checklist. Data will be analysed in SPSS (v23, IBM) and R studio (R. RStudio, Boston, MA, USA). To conform to the exploratory nature of the work, descriptive statistics such as means, and ranges will be used here based on the number of participants stratified across 4 teams. Independent t-tests will further explore any observable differences. Those data will be complimented with simple plots. Anonymised data will be made available on reasonable request.

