## **Simulation**

Prior to each simulation, participants will receive briefing about features of simulation dolls (i.e., to mimic the patient), how they need to assess the doll, and what information they need to obtain from the simulation instructors. Before each scenario each team will have approximately five minutes to prepare for the simulation. We will have two scenarios, one with management of an extreme preterm infant and another with the management of a term newborn with complications at delivery. Details of term and preterm resuscitation scenarios are provided in Appendix-1 and Appendix-2. Both these scenarios were used previously in our neonatal unit simulations. Both the simulation scenarios will need endotracheal intubation with the term baby scenario needing chest compression and umbilical vein administration of epinephrine. We will use the SimNewB (Laerdal Medical, Laerdal, Stavanger, Norway) low

HUFIN\_V5\_March 2022 IRAS: 314695 10

fidelity manikin for term and Premature infant Anne-low fidelity (Laerdal Medical, Laerdal, Stavanger, Norway) for the preterm scenarios, respectively. The two scenarios will be the same for all participants. We will run the two simulation scenarios with three different teams, giving a total of 6 scenarios. Each scenario will be running approximately for 10-15 minutes.

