## **Briefing**

All scenarios will be preceded by locally developed standardised briefing including checklist of role allocation, equipment checking, and escalation plan. Most neonatal units will have this kind of checklist with some modifications to suit local set up. All the airway operators will be briefed about using eye-tracking wearable and undergo pre-simulation test for familiarity. Briefing will be done by the team leader, and we will use a local unit briefing checklist (Appendix-3).

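### The protocol gives 18 and 24 participants and 3 and 4 teams, but four-person teams yield 12 or 16 people, so neither participant figure can be a head count

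*Protocol*

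**What the plan says.** The size of the study appears in several places in the protocol, with different values.

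- **Sample size:** "we will need to conduct 6 scenarios with 3 samples in each group (equalling 18 participants". The inputs are "In this study operator spent 35% (SD 8) of time focused on the infant", a target described as "to improve the VA on the infant to 55" per cent, and "with 80% power and alpha error of 0.05".
- **Statistics:** "Therefore, our anticipated dataset size of 24 participants, will provide greater insight to examine VA behaviour differences". Descriptive statistics are to be "based on the number of participants stratified across 4 teams". The number of groups is printed as XXX. The comparator is a pilot with 6 eye-tracking recordings of 5 minutes.
- **Simulation:** "We will run the two simulation scenarios with three different teams, giving a total of 6 scenarios". Each run lasts about 10 to 15 minutes. Study algorithm repeats 3 teams and 6 runs, and has each team do one run with a leader and one without.
- **Participants (Team selection):** a team is one nurse, one tier-1 member and two tier-2 members.
- **Briefing:** "All the airway operators will be briefed about using eye-tracking wearable and undergo pre-simulation test for familiarity". Table S2, by contrast, has visual attention columns for nurse, tier-1 and tier-2.

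**The concern.** The participant totals disagree with each other, the team counts disagree with each other, and neither total fits the team composition. A reader cannot tell how many people are to be recruited, how many runs there will be, or how many observations the powered comparison has.

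Three things are at stake. The recruitment target is undefined. The justification in Statistics, which sets 24 participants against a pilot with 6 recordings, rests on a count the design cannot produce. And because every team is run twice, a total above the number of people must contain repeats. If those repeats were later analysed as separate participants, the result would look more precise than it is.

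**Working it through.** **1. Reproduce the Sample size figure.** Inputs from that section: difference 55 − 35 = 20 points, SD 8, power 80%, alpha 0.05. Sidedness is not stated; two-sided is assumed.

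n per group = 2 × (1.960 + 0.842)² × 8² / 20² = 2 × 7.85 × 0.16 = 2.5, rounded up to 3.

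The 3 samples per group are therefore reproduced by the normal approximation (one-sided it would be 2). Two groups of 3 are 6 observations. No step in this calculation leads to 18 participants.

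**2. Count people.** Team size from Participants: 1 + 1 + 2 = 4. Assume nobody serves in two teams.

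| | 3 teams | 4 teams |
|---|---|---|
| Distinct people (teams × 4) | 12 | 16 |
| Runs (teams × 2) | 6 | 8 |
| Person-recordings, 3 tracked per run | 18 | 24 |
| Person-recordings, 4 tracked per run | 24 | 32 |
| Operator recordings, one per run | 6 (3 per condition) | 8 (4 per condition) |
| Distinct operators | 3 to 6 | 4 to 8 |

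Neither 18 nor 24 appears in the row of distinct people. Both appear among the person-recordings: 18 = 6 × 3, and 24 = 6 × 4 or 8 × 3. Relative to 12 people the stated totals are 18/12 = 1.5 and 24/12 = 2 times too large; relative to 16 they are 1.1 and 1.5 times.

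**3. Operators.** The lower end of each operator range has the same person managing the airway in both of the team's runs, as Primary aims and the same-person columns of Table S2 suggest. The upper end has a different person each time, which is possible because the protocol does not fix the operator and each team has two tier-2 members.

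**4. Compare with the pilot.** The pilot had 6 recordings × 5 min = 30 min. With 3 teams the operator comparison has 6 recordings × 10 to 15 min = 60 to 90 min. The number of recordings is equal; the recorded time is longer.

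**5. Precision on the operator recordings.** SD 8, 3 per condition, 95% interval:

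- Unpaired: t(4) × 8 × √(2/3) = 2.776 × 6.53 = 18.1 points.
- Paired, 3 operators, correlation 0.5 (an assumption; the protocol gives none): the SD of the difference is 8 × √(2 × 0.5) = 8, so t(2) × 8/√3 = 4.303 × 4.62 = 19.9 points.

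**6. Side check.** With the planned independent t-test, exact two-sided power at 3 per group is 63.6%, and 4 per group are needed to pass 80% (83.6%). This treats the two groups as independent, which they are not if the operator is the same person. For a paired test on 3 operators, power is 40% at correlation 0, 62% at 0.5, 79% at 0.7 and 90% at 0.8.

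**The case against.** The contradictions themselves have no defence in the text. The objections concern what can be built on them, and most of them stand.

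- **Origin of 18 and 24.** A reader might infer that both totals count the same people twice over 6 runs. That needs a multiplier of 3 for one figure and 4 for the other. Six per team explains both equally well: 3 × 6 = 18 and 4 × 6 = 24, for instance three tracked roles in two runs, matching the role columns of Table S2. The only disagreement left would then be 3 against 4 teams. Six-member teams would also give both figures, but contradict Participants. The origin is therefore an inference.
- **Three operators as the primary analysis set.** A reader might infer this from Briefing, which mentions only airway operators. But Primary aims speaks of an operator or member, Outcomes defines the primary outcome over participants, anyone unwilling to wear the device is excluded, and Table S2 reports all three roles. Who wears the tracker is unsettled, and so is whether the operator is the same person in both runs.
- **The pilot comparison as simply false.** The sentence speaks of dataset size and of visual attention in general. Longer runs, and possibly more wearers, could yield more data than the pilot. What is wrong is the figure of 24 participants, and any suggestion of more recordings for the operator comparison with 3 teams.
- **A falsely narrow interval.** Entering 18 or 24 independent values at SD 8 would give half-widths of 8.0 or 6.8 points. No section says this will be done, Sample size powers the comparison on 3 per group, and SD 8 is an operator figure that need not hold for other roles. These two half-widths show a risk and do not describe the plan.

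The study is also described as exploratory, with descriptive statistics first. That lowers the inferential stakes but does not make the counts agree.

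**Conclusion.** The point holds as a matter of inconsistent and unattainable counts. The protocol states 18 and 24 participants and 3 and 4 teams, and leaves the number of groups blank; with its own team composition the head count is 12 or 16. The power inputs support 3 observations per group, 6 in total, and do not lead to 18 participants.

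If there is one airway operator per run, the comparison on which the study is powered has 6 recordings, 3 per condition, from 3 to 6 people with 3 teams. It then has no advantage in number of recordings over the pilot.

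This rests on four-person teams, no one serving in two teams and one operator per run. The half-width of about 18 points also assumes SD 8 in both conditions and unpaired data; the paired figure of about 20 points assumes a correlation of 0.5. The documents do not establish how 18 and 24 arose, that only operators wear the tracker, or that repeated recordings will be analysed as independent.

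**What to change.** Choose the number of teams, then state one set of figures and use it in Simulation, Study algorithm, Sample size and Statistics:

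- **3 teams:** 12 people, 6 runs, 3 operator recordings per condition; or **4 teams:** 16 people, 8 runs, 4 operator recordings per condition.
- Say who wears the tracker in each run, and whether the airway operator is the same person in both of a team's runs.
- Tie the power statement to operator recordings. If 18 or 24 is kept, call it person-recordings, show the multiplication, and state that repeated recordings of one person are not treated as independent participants.
- Replace XXX. First reconcile the research question under Study, which has leader and no-leader conditions each with and without a pre-briefing, with Briefing, which has every scenario briefed.
- Restate the comparison with the pilot using the corrected count, giving number of recordings and recorded time separately.
- If a precision figure is given, base it on the operator recordings and state the correlation assumed for any paired version.

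The choice of teams also bears on the balance claimed in Study algorithm. With 3 teams each scenario is run three times and can only split 2:1 between leader and no leader; with 4 teams it can split 2:2.

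The cost is protocol wording. Correcting the figures for 3 teams adds no participants; choosing 4 teams would need 4 more people than the 12 that 3 teams provide, and two more runs.

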#### Primary aims:

To compare the VA of a team operator/member when s/he:

- 1) Is managing airway and acting as team leader and
- 2) Has a dedicated team leader.

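### The descriptive results are stratified by team, not by leader condition within scenario, so the named strata do not show the primary contrast

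*Protocol*

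**What the plan says.** The primary aim is a contrast of leader conditions: "To compare the VA of a team operator/member when s/he" manages the airway and also leads, against having a dedicated leader. The Study algorithm sets out a two-run design: "Each team will participate in two simulation scenarios (i) term and (ii) preterm", and "Each team will undergo one scenario with a team leader and another scenario without a team leader". It also states that "The sequence in which each team is allocated with/without team leader would be alternating with each team", and that "With 3 teams, there will be total of 6 simulation experiments". It adds that alternation will give each scenario as many runs with a leader as without.

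The Statistics section introduces its descriptive plan with "To conform to the exploratory nature of the work" and then says that "descriptive statistics such as means, and ranges will be used here based on the number of participants stratified across 4 teams". It continues: "Independent t-tests will further explore any observable differences". That sentence names no grouping factor, and the number of groups earlier in the section is an unfilled placeholder.

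Table S2, the layout for the gaze outcomes, has two blocks. One covers all scenarios (between participants) and the other is a within-team, same-person comparison. Both are split by role (nurse, tier-1, tier-2). Neither has columns for leader condition or scenario.

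**The concern.** A stratifier helps when the factor of interest differs between strata, or is compared inside each stratum with other things held equal. Team does neither here. Leader condition varies within every team, so it does not distinguish one team from another. Inside a team, leader condition changes together with scenario, so the two runs are not like for like.

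The scenarios are not interchangeable. The Simulation section says that only the term case needs chest compression and umbilical vein epinephrine. Procedures and team members are among the areas of interest for gaze, so a scenario difference in visual attention is plausible. The Protocol gives no figure for its size.

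At stake is whether a small exploratory study shows its main contrast clearly, or leaves the reader with team summaries and same-person differences in which a scenario difference can pass for a leader effect. The same applies to team performance and workload.

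**Working it through.** **Inputs.** The Sample size section gives 35% of time on the infant without a dedicated leader (SD 8) and 55% with one, so the planned leader effect is L = 55 − 35 = 20 points. Its figure of 3 per group reproduces by the two-sided normal formula: 2 × 8² × (1.960 + 0.842)² / 20² = 2.51, rounded up to 3. That calculation compares leader conditions, not teams. Let b be the preterm mean without a leader, and S the term-minus-preterm difference, assumed additive. S is not in the Protocol; I use 5, 10 and 20 points as an illustrative range. The Protocol does not say whether all teams take the scenarios in the same order. If they do, any order effect is part of S.

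**Step 1: team summaries.** A team with its leader in the preterm run has values b + L (preterm) and b + S (term). A team with its leader in the term run has b and b + S + L. If a team's two runs are pooled, the mean is b + L/2 + S/2 in both cases. With b = 35, L = 20 and S = 0 this is 45 for every team; with S = 10 it is 50 for every team. Comparing teams carries no information on L.

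**Step 2: within-team contrasts.** With minus without leader:

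- leader in preterm: (b + L) − (b + S) = L − S
- leader in term: (b + S + L) − b = L + S

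| Assumed S | Leader in preterm | Leader in term |
|---|---|---|
| 5 | 15 | 25 |
| 10 | 10 | 30 |
| 20 | 0 | 40 |

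One team supplies two runs for three unknowns (baseline, leader, scenario), so L cannot be estimated from one team.

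**Step 3: across teams.** Three alternating teams give 6 runs for 5 unknowns (three team levels, leader, scenario), and the design matrix has full rank 5. Four teams give 8 runs for 6 unknowns, rank 6. The leader effect is therefore estimable across teams in either case.

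**Step 4: the simple with/without mean.** With three teams each scenario has three runs, so the counts with and without a leader cannot be equal; they are 2:1. If two teams have the leader in preterm:

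- mean with leader: [2(b + L) + (b + S + L)] / 3 = b + L + S/3
- mean without leader: [2(b + S) + b] / 3 = b + 2S/3
- difference: L − S/3

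For S = 5, 10 and 20 this is 18.3, 16.7 and 13.3 against a true 20. The shifts are 1.7, 3.3 and 6.7 points, and their sign reverses if two teams have the leader in term. With four alternating teams the split is 2:2 and the simple difference equals L for any S.

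**Step 5: leader condition within scenario.** The preterm difference is (b + L) − b = L and the term difference is (b + S + L) − (b + S) = L, so S drops out of each. Within one scenario the two conditions come from different teams, so team differences enter. With three teams these add d to one scenario's difference and subtract d from the other, where d is the mean level of the two same-sequence teams minus that of the third. The equal-weight average is [(L + d) + (L − d)] / 2 = L. Both S and d cancel.

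**The case against.** The strongest reply is that the sentence does not prescribe tables by team. It can be read as describing how participants are spread over teams, and nowhere says that a team's two runs are pooled. The t-test sentence names no groups, and the surrounding text points to leader condition: the primary aim, the 35% against 55% planning contrast, the Statistics section's stated interest in the impact of a team lead, and the SPIRIT figure, which labels its two assessments with and without a leader. Table S2 has no team columns, and its same-person block is in effect a comparison of the two leader conditions. Alternation is there to deal with scenario. Table layouts are often left to a statistical analysis plan.

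Most of this stands. A reader might infer that the study will average its leader effect away, that every team will report 45%, that the t-tests will compare teams, or that the main tables cannot show the effect. The documents support none of these as stated rules. Each needs the assumption that runs are pooled by team or that team is the t-test grouping, and the design itself keeps the effect recoverable.

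Two things remain. The Protocol does not simply leave the layout open: it names a stratifier, and that stratifier is not the comparison of interest. And the same-person block of Table S2 is the contrast in which leader and scenario change together, while the other block covers all scenarios without separating them. Alternation helps only if the summary uses it, and with three teams it cannot deliver the equal counts that the Study algorithm expects.

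**Conclusion.** The point holds as a matter of how the results are laid out and combined, not as a flaw that makes the leader effect unrecoverable. Team is the only stratifier named for the descriptive results, and nothing in the Protocol tabulates by leader condition within scenario. Summaries by team are uninformative about the primary contrast, and each within-team or same-person contrast is off by the whole scenario difference, in one direction or the other according to sequence. With three teams, a simple with/without mean is off by one third of it, about 3.3 points for an assumed 10.

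These sizes rest on an additive scenario effect and on assumed values of S; if S is zero, the shifts vanish. On the looser reading of the sentence, the section names no comparison factor at all for its descriptive output, and the same correction is needed. It should be made before analysis.

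**What to change.** In the Statistics section, replace the stratification by team with summaries by leader condition (with, without) within scenario (term, preterm). State that the two scenarios are combined with equal weight, or that the leader effect is adjusted for scenario.

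In Table S2, keep the split by role, add with-leader and without-leader columns, and separate the scenarios. Show each team's two runs as a linked pair in the plots. Where a cell holds only one or two runs, list individual values in place of means and ranges: per run for team performance and operator gaze, per participant for NASA-TLX. Use the same layout for all three outcomes.

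Reconcile the number of teams separately: the Simulation and Study algorithm sections say three, the Statistics section says four. Three teams give cells of one or two runs; four would give two in each.

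The cost is a sentence and a table layout, with small cells that must be shown as such. No new data are needed.
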